### Intervention

Index participants who are randomized to the intervention arm will be invited to form a microclinic group. As described above, study staff will assist participants in microclinic group formation in a confidential manner. Though groups are formed from the social networks of index patients, group members will not be made aware of the specific process by which groups are formed or the identiy of the index patient or patients within any given group. This procedure protects against unintended breach of confidentiality and also allows groups to focus on the health of all members rather than specific index group members.

Following group recruitment, newly formed groups will attend an orientation meeting. This meeting will provide an overview of the microclinic intervention, as well as time for ‘social network’ participants to enroll in the study, complete baseline data collection and participate in baseline HIV voluntary counseling and testing (see enrollment procedures in Section VIII.d).

Following the orientation meeting, all microclinic groups will progress through a series of six microclinic sessions. (Appendix J) Sessions will take place every two weeks, will be led by trained community health workers and will take place at a time and location of the group’s choosing. Study staff will provide training for the community health worker facilitators and will supervise facilitation to ensure that the intervention is delivered as intended. Session topics for the seven sessions are as follows:

1. Overview of HIV biology and Scope of HIV on Lake Victoria
2. HIV medication overview – how medications work and why they are important
3. Antiretroviral therapy and herbal medicine
4. Destigmatization and group social support
5. Being an active patient
6. Confidentiality

[Group disclosure]

1. Post-group disclosure debriefing and the way forward

Following completion of the sixth group session, microclinic group members will be offered the opportunity to participate in Voluntary Counseling and Testing and group HIV status disclosure to other microclinic group members. Participation will be strictly voluntary and the sixth microclinic session will extensively cover the topic of group confidentiality and the importance of not pressuring or stigmatizing group members who do not want to participate in the process.

### Measurements

The predictor of interest is the baseline treatment assignment, as determined by randomization. All analysis will be conducted using an intention-to-treat analysis.

Covariates of interest will be collected through participant surveys at baseline and study closure, as well as routine clinic data collected at the participant’s original clinic and any other clinics from which he or she receives HIV care during the course of the study. Baseline surveys (Appendix C) will collect data related to the following:

1. Demographic characteristics
2. Contact and locator information
3. HIV-related stigma[23](#_ENREF_23)
4. HIV status disclosure
5. Social support
6. Clinic data (date first HIV positive, date of enrollment)
7. Reason for missed clinic appointment, including name of other facilities where care was received

At the end-of-study survey (Appendix G), additional data will be collected related to possible adverse events that may or may not be related to the intervention. In addition to specific questions in the survey, an open-ended question will be used to assess other adverse experiences related to issues such as stigma, unintended disclosure or poor treatment by health center staff. Participants will be asked whether they attribute any or all of these experiences to participation in the study. Additionally, participants in the intervention arm will specifically be asked about adverse experiences related to group status disclosure, again using both a checklist and an open-ended question. At the end-of-study survey, patients will be asked if they are currently in care and, if so, which clinic. Reasons for transfer or disengagement from the original clinic will be assessed. For patients who were lost-to-follow-up (missed a clinic visit by ≥90 days and did not return to clinic) or who transferred out from their original clinic, a patient tracing survey will also be conducted. (Appendix F) See description of clinic data capture below regarding determination of patient’s visit history and transfer status.

In addition to survey data, clinical data will also be collected for all study participants. Chart review will be conducted at participant’s clinic of origin to collect data on baseline disease status, and clinical and laboratory data over the course of the study (CD4 count, WHO stage, viral load). Other clinical data will include date of first HIV test, date of clinic enrollment, date of ART initiation (if applicable), complete visit history, patient tracing visits conducted by clinic staff, patient death and patient transfer. For patients who transfer to other sites, study staff will visit that site to confirm that transfer occurred and obtain the above clinic data available for the patient after the transfer (either through physical chart review or the OpenMRS electronic medical record). Data obtained from clinics will be limited to data that was collected during routine patient care.

Qualitative Data Collection

Focus Group Discussions:

Twelve (12) focus group discussions will be conducted at the conclusion of the intervention phase of the study. It will be reiterated to all participants that focus group participation is completely voluntary and that refusal to participate as well as any issues discussed within the focus group will have no effect whatsoever on relationships with FACES and OHR. All FG participants will complete a separate Qualitative Consent Form (Appendix K). Each Focus group will follow the discussion protocol outlined in Appendix L – Focus Group Discussion Guide.

- - - Eight (8) focus group discussions with study participants (5-15 people each). A convienience sample of participants will be identified and selected by research staff during enrollment, and follow-up, based on availability and interest in participating in Focus Group discussions.
    - Two (2) focus group discussions with CHW Facilitators who lead and conduct the micro-clinic training program.
    - Two (2) focus group discussions with the FACES/OHR staff implementing the Microclinic intervention.

Discussions will investigate issues of care and treatment utilization and HAART adherence, social support, local HIV attitudes, microclinic participation, and community mobilization strategies. The target size of the discussions will be 8-12 participants. Group discussions will be facilitated by a trained research team member and a note-taker/translator. The discussions will be audio-taped and transcribed. Finally, the collection of qualitative data may extend beyond these focus groups. If emerging data points to particular concerns or needs of individuals in the focus group, then we will conduct in-depth semi-structured interviews with particular focus group participants or schedule an additional focus group discussion. All data from FG discussions will be de-identified be kept anonymously to protect participant confidentiality.

Semi-Structured Interviews

A convenience sample of between 25 and 50 study participants to participate in informal, semi-structured interviews with trained research staff. Research staff will recruit an equal number of participants from intervention and non-intervention arms. Semi-structured interviews will be scheduled in a private location at the convenience of study participants, either at the clinic, community center or home. All interviews will be conducted by trained local research staff in Luo, Swahili or English, per subject preference, using an open-ended interview format. Participants will be given the opportunity to comment on three major topics 1) their experience regarding engagement with HIV care and treatment on Mfangano Island, 2) challenges faced, and 3) opportunities for improvement. Study subjects who participated in the microclinic intervention will be given an opportunity to provide critical, anonymous feedback. Notes and audio recordings will be maintained and secured at the local research facility. All data from semi-structured interviews will be de-identified be kept anonymously to protect participant confidentiality. Discussion guides for these semi-structured interviews can be found in Appendix M. Participants in semi-structured interviews will complete a separate informed consent document prior to initiating the interview (Appendix K).

Participant Observation

Trained social scientists from the University of California in San Francisco, along with qualified local research staff will also participate in MC training workshops throughout the island, living within the Mfangano Island community for the duration of the study. These research staff will work with FACES and OHR staff to implement the program and gather anonymous observations and feedback from participants and community members. Formal participant observations will be documented to aid in the interpretation and discussion of study results at the conclusion of the study.

### Data Verification and Security

All data will be collected by study staff trained in Good Clinical Practice procedures and Human Subjects Protection. Training will be conducted independently by an on-site co-investigator and through internet-based courses with the NIDA Clinical Trials Network and the National Institutes of Health. Training will be renewed on an annual basis during the duration of the trial.

All personal identifying information (name, date of birth, phone number, locator information, medical record number) will be collected on a hard copy form that will be separate from the rest of the survey data that will be collected on elecronic tablets. Identifying information will be linked to electronically-captured study data only through a unique identifier that is assigned by the study and carries no meaning outside the study. Indentifying information will be stored in separate locked file cabinets in the Ekialo Kiona Center Research Department. De-identified electronic data will be collected using password protected tablets and will be encrypted and uploaded to a secure server. Tablets will be stored in the study office, which will remain locked any time an authorized study staff member is not present. Furthermore, the Ekialo Kiona center is under survelliance 24 hours per day, 7 days per week by a trained security guard to ensure that there is no unauthorized access to the facilities or to confidential research documents.

Data collected at the health facilities will be entered into a password-protected Microsoft Access database on a password protected laptop. Where possible, clinical data will be cross-checked against electronic medical record data obtained from the FACES OpenMRS database.

### Adverse Events

All study participants in both study arms will be asked to complete an end-of-study survey. This survey will include an open-ended questions about any adverse events experienced over the course of thes study (Appendix G). Risk of any adverse event will be compared between index participants in the two study arms, and risk of adverse events will be described among ‘social network’ members who participated in the microclinic intervention. All participants reporting an adverse event will be offered counseling by a trained VCT counselor and/or a staff member at the participant’s preferred health facility.

In addition to self-reported adverse events, clinic staff will also review participant medical records on a monthly basis. Appendix N outlines study procedures for reporting adverse clinical events to the KEMRI Ethical Review Committee.

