# List of Appendices

1. Eligibility Determination Form
2. Participant Locator Information Form
3. Baseline Participant Survey Form
4. Microclinic Group Member Survey Form
5. Microclinic Group Information
6. Loss To Follow-Up Tracing Form
7. End of Study Participant Survey Form
8. Index Participant Consent Document
9. Microclinic Group Member Consent Document
10. Microclinic Curriculum Overview
11. Qualitative Consent Document
12. Focus Group Discussion Guide
13. Semi-Structured Interview Guide
14. Severe Adverse Event Reporting

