| F1. In the last 6 months, I received assistance/support from friends or family in attending my HIV clinic appointments |  |  |  | |  |  |
| F1b. Please check all types of support received: |  Encouragement   Reminders   Financial assistance   Transportation (non-financial) | | |  Help with duties at home (i.e. childcare, chores)   Help with duties at work   Accompanyment (i.e. someone goes with me to my appointments) | | |
| F2. In the last 6 months, I received assistance/support from friends or family in taking my HIV medications |  |  |  | |  |  |
| F2b. Please check all types of support received: |  Encouragement   Reminders   Gives me food to take with medications   Advice about side effects | | |  Observation (someone watches me take my medications)   Accompanyment (someone takes their medications with me at the same time) | | |

| **SECTION G. KANYAKLA INFORMATION** | | | | |
| --- | --- | --- | --- | --- |
| G1. Did you participate in a kanyakla group? | | | | |
|  Yes | G1a. What is the name of your kanyakla? | | |  |
| G1b. Did you participate in group VCT? | | | |
|  Yes | G1c. What were the reasons why you decided to participate in group VCT? *(check all that apply)* | | |
|  I had not disclosed to my group before, but wanted them to know my status.   Group VCT was not the first time I was disclosing my status - I have already shared my status within my group.   Group VCT was not the first time I was disclosing my status - I have already shared my status to many people in the community.   I did not want to participate in group VCT but my kanyakla pressured me to participate.   Other, specify: | | |
| Describe details of response: | | |
|  No | G1d. What were the reasons why you decided NOT to participate in group VCT? *(check all that apply)* | | |
|  I did not want my group members to know my status.   I was afraid my group would not keep my status confidential.   I did not think group VCT was important to attend.   Other, specify: | | |
| Describe details of response: | | |
|  No | G1f. Were you offered a chance to join a kanyakla? *If participant is confused by this question, explain that you have not been told who has and has not been offered a chance to join kanyakla. This helps you make sure to get people’s answers as accurately as possible without making any assumptions.* | | | |
|  Yes | G1g. What were the reasons that you decided not to join? | | |

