**Severe Adverse Event Reporting**

Severe adverse events, including death from any cause and hospitalization not related to trauma or pregnancy, occuring among study participants during study enrollment will be reported to the KEMRI Ethical Review Committee within stated KEMRI reporting guidelines.

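### The protocol compares adverse-event risk between arms, but the end-of-study form shown does not ask about adverse events, and the text adds extra prompts for the intervention arm alone

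*Protocol*

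**What the plan says.** Under Procedures, the Adverse Events subsection plans that "Risk of any adverse event will be compared between index participants in the two study arms". It places the source in the end-of-study survey: "This survey will include an open-ended questions about any adverse events experienced over the course of thes study (Appendix G". It adds a monthly review of medical records by clinic staff.

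The Measurements subsection describes a fuller instrument in the same survey: "In addition to specific questions in the survey, an open-ended question will be used to assess other adverse experiences". Its examples are stigma, unintended disclosure and poor treatment by health-centre staff. Participants are also to be asked whether they attribute such experiences to the study. It then adds that the "intervention arm will specifically be asked about adverse experiences related to group status disclosure, again using both a checklist and an open-ended question".

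The List of Appendices gives the seventh appendix, G, as the "End of Study Participant Survey Form".

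Appendix N lists the severe events to be reported to the ethics committee: death from any cause, and "hospitalization not related to trauma or pregnancy".

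**The concern.** Harm is asked about once, at study end. If the form in use lacks the questions, no later analysis decision can recover the answers. The gap falls where it matters most: Ethical Considerations names loss of confidentiality and reputational damage from unintended disclosure as the main risk of the study, and the intervention works by facilitating disclosure within social networks. The offer of counselling to participants who report an adverse event depends on the same questions.

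The second worry is unequal ascertainment. A comparison of any adverse event is fair only if both arms are asked the same things. Extra prompts in one arm can add reports in that arm and cannot remove any.

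**Working it through.** **Text against form.** The protocol gives no figure for this comparison, so there is none to reproduce. The check sets what the text promises beside the form.

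| Promised in Measurements or Adverse Events | On the Appendix G form shown |
|---|---|
| Specific adverse-event questions, both arms | None |
| Open-ended adverse-event question, both arms | None |
| Attribution to study participation | None |
| Checklist and open question on group-disclosure harms, intervention arm | None; Section G has one tick-box about being pressured by the group |

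The form runs in unbroken lettering: A administrative, B missed visits, C disclosure, D stigma, E social network, F support for care, G kanyakla information. The nearest items are these:

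- Section C asks whom the participant has told. It does not ask about disclosure against the participant's wishes.
- Items D16 to D24 ask both arms how often family, community health workers and healthcare workers have treated them badly because of HIV. They are a frequency scale about the past, not tied to the study period, with no attribution.
- Section G opens with "Did you participate in a kanyakla group". The pressure tick-box is one listed reason for taking part in group testing, so only people who joined a group and took part can reach it.

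**Size of the possible asymmetry.** The inputs are:

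- *p*, the risk reported on items common to both arms: assumed 5%, 10% or 20%.
- *q*, the chance that an intervention participant with nothing on the common items reports something on the extra items: assumed 2%, 5% or 10%.
- *N* = 180 per arm, the upper target in Sampling (2 × 180 = 360).
- Alpha = 0.05, as in the sample-size section; two-sided is assumed.

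Reported risk is *p* in the control arm and 1 − (1 − *p*)(1 − *q*) in the intervention arm. With *p* = 10% and *q* = 5% this is 1 − 0.90 × 0.95 = 0.145, a ratio of 0.145/0.10 = 1.45 and a difference of 4.5 points.

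The chance of a significant result uses a pooled two-proportion z-test. For that example the mean risk is 0.1225. The standard error under the null is √(2 × 0.1225 × 0.8775/180) = 0.0346, and under the stated risks it is √((0.10 × 0.90 + 0.145 × 0.855)/180) = 0.0345. The upper tail is Φ((0.045 − 1.96 × 0.0346)/0.0345), about 0.255; the other tail is negligible.

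| *p* | *q* | Intervention arm, reported | Risk ratio | Chance of p < 0.05 |
|---|---|---|---|---|
| 5% | 2% | 6.9% | 1.38 | 11.8% |
| 5% | 5% | 9.75% | 1.95 | 40.7% |
| 5% | 10% | 14.5% | 2.90 | 86.3% |
| 10% | 2% | 11.8% | 1.18 | 8.5% |
| 10% | 5% | 14.5% | 1.45 | 25.5% |
| 10% | 10% | 19.0% | 1.90 | 68.0% |
| 20% | 2% | 21.6% | 1.08 | 6.6% |
| 20% | 5% | 24.0% | 1.20 | 15.0% |
| 20% | 10% | 28.0% | 1.40 | 42.7% |

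At 156 per arm the last column runs from 6.4% to 81.1%. With *q* = 0, when only common items count, it is the nominal 5%.

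**The case against.** The strongest reply is that the text describes a sound design and only the form lags behind. Measurements gives both arms specific questions, an open question and an attribution question. The word *again* in the sentence on the intervention arm implies that the common block has a checklist too, so the intervention-only items are a supplement. Nothing says the supplement counts towards any adverse event, and an analysis plan that is not at hand may settle it. Harm from group disclosure can arise only where group disclosure is offered, so some extra reports would be genuine. Adverse-event risk is also not among the primary or secondary outcomes.

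Much of this stands, and it rules out several stronger readings that a reader might infer:

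- *That the comparison cannot be valid.* The documents do not support this. Restricted to items asked identically in both arms, it would be valid once the form carries them.
- *That the trial would hold no self-reported harm data.* The stigma scale is asked of both arms at baseline and at study end and touches two of the three example domains, stigma and staff treatment. Record review covers both arms as well. Neither asks participants about unintended disclosure or attribution.
- *That the excess in the table is a forecast, or wholly spurious.* Both inputs are assumed, and genuine disclosure harm would appear in the same column.
- *That the trauma exclusion undermines the comparison.* Appendix N governs reporting to the ethics committee, applies equally to both arms and still covers death from any cause. Its list is introduced as inclusive, so it may not be exhaustive.

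One caution concerns completeness. Consent pages were removed from the appendices, and item numbering in Section G skips from G1d to G1f. Section G nevertheless reads as the end of the form, and a missing adverse-event section is unlikely to be an effect of text extraction.

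What the reply does not answer is the mismatch itself. An analysis plan can define the endpoint, but it cannot supply questions that were never asked.

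**Conclusion.** The concern holds in a limited form. Measurements and Adverse Events describe questions that the Appendix G form shown does not contain. Used as shown, the form would leave the planned comparison without its stated survey data. This rests on the printed form being complete.

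The risk of unequal ascertainment is conditional. It arises only if the intervention-only items count towards any adverse event, which the protocol leaves open. Its direction would be against the intervention. Its size is unknown: over the assumed ranges, risk ratios of 1.08 to 2.90 and a chance of a significant difference of about 6% to 86% instead of 5%, if risk on the common items is equal.

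A separate reporting gap also stands: under the Appendix N wording, a non-fatal admission after disclosure-related violence is not among the listed reportable events.

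**What to change.** 1. Reconcile Appendix G with Measurements and Adverse Events by adding one identical adverse-event block for both arms: a checklist, an open question and an attribution question. The checklist should cover at least the domains Measurements already names, including unintended disclosure.
2. State in Adverse Events that the between-arm comparison uses only items asked identically in both arms.
3. Report the group-disclosure items descriptively in the intervention arm.
4. Separately, the sponsor should reconcile the trauma exclusion in Appendix N with the disclosure risk named in Ethical Considerations.

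The cost is a form revision made before the end-of-study survey begins, one added sentence in Adverse Events, clarification of Appendix N, a few more interview minutes per participant and possibly a few more reports to the ethics committee.

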## Sampling

*Sample Size Calculation*

Sample size calculations were generated based on preliminary data from the Mfangano Island Healthy Network Impact Study (MIHNIS). The MIHNIS study was a quasi-experimental study with the intervention delivered to one community and neighboring communities acting as control groups. Additionally, the proposed clinic sites were visited in September 2014 to assess rates of missed clinic appointments to help ground sample size estimates in the realities of each individual clinic.

During the six months prior to delivery of the intervention in the MIHNIS study, 268 of 410 (65%) patients on ART at the Sena Health Center missed a clinic visit by >3 days. Of these, 238 (89%) joined the study. Among the control group in the MIHNIS study, 36 of 145 (25%) participants who missed a clinic visit by more than 3 days during the 6 months enrollment period had a 90-day clinic absence within the following 12 months. Among patients eligible for the intervention and who missed a clinic visit by >3 days during the enrollment period, 72 of 93 (77%) actually participated in the microclinic intervention. In the MIHNIS study participants in the intervention community had a more than 50% lower rate of 90-day disengagement than those in the control community, regardless of intervention uptake.

Thus, we assume an event rate of 0.25 in the control group and 0.125 in the intervention group. Setting alpha to 0.05 and beta to 0.2 and assuming an average of 2 participants per group with a coefficient of variation of 0.25, we will need 156 index participants per study arm. This sample size accounts for non-independence of outcomes introduced by the clustered nature of the intervention. Allowing for 10% participant attrition, we would need to sample 175 participants per study arm. The MIHNIS study ascertained outcomes for 98.6% of study participants, thus the allowance for 10% attrition in the proposed study is conservative.

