A full clinic visit history will be obtained for all study participants on HIV care and treatment at any of the included study sites. Visit history data will be obtained from the FACES-MOH “Blue Cards”. For patients who made an official tranfer to another facilities within Nyanza Province, study staff will visit that facility to confirm the transfer and obtain a complete clinic visit history following the transfer. In addition to data on clinic visit attendance, patient enrollment date, ART initiation date, ART regimen, CD4 measurements, viral load measurements, pharmacy pick up, vital status and locator information will also be collected. All participants lost to follow-up from clinical care during the course of the study will be traced to ascertain vital and clinical status (i.e. disengagement from any clinical care, transfer to another facility, death while ‘in care’ or death after disengaging from care). For patients who made an unofficial transfer to another health facility in Nyanza Province, study staff will visit that facility to obtain visit history as was described for the official transfers. For patients who are disengaged from clinical care at the time of tracing, barriers to return to care will be identified and participants will be counseled to return to care. Clinic staff will be informed of any additional information gained in the field regarding the vital or clinical status of patients who were lost to follow up from clinical care.

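### As written, the between-arm adverse-event comparison appears to rest on the end-of-study survey, and deaths are nowhere compared between arms as a harm

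*Protocol*

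**What the plan says.** Protocol VIII.F, Adverse Events, opens with the survey: "All study participants in both study arms will be asked to complete an end-of-study survey". It mentions the survey's adverse-event question, then states the comparison: "Risk of any adverse event will be compared between index participants in the two study arms". The same sentence adds a description of risk among social network members, and the paragraph ends with counselling for those who report an event.

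The next paragraph adds a second stream: "In addition to self-reported adverse events, clinic staff will also review participant medical records on a monthly basis". Its stated destination is the ethics committee: "Appendix N outlines study procedures for reporting adverse clinical events to the KEMRI Ethical Review Committee". Appendix N defines what is reported there: "Severe adverse events, including death from any cause and hospitalization not related to trauma or pregnancy".

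The Measurements section also places adverse-event collection at the end-of-study survey, where "additional data will be collected related to possible adverse events that may or may not be related to the intervention". The Study Design Overview says that participants lost to follow-up from care "will be traced to ascertain vital and clinical status", with death while in care distinguished from death after disengagement.

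In Data Analysis (VIII.G), death is a competing event in the cumulative incidence curves for Hypotheses 1 and 3. It counts as failure in the alive-and-retained proportion (Hypothesis 4) and the alive-and-suppressed proportion (Hypothesis 5).

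**The concern.** A survey at study closure can be answered only by someone who is alive, found and willing. If the compared risk is built from it, the safety comparison is made among surveyed survivors. Death, which Appendix N names first among severe adverse events, then falls outside the one between-arm harm comparison in the plan.

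The protocol names unintended disclosure and damage to reputation as the main risk. People harmed in that way may be among those who leave or avoid study staff, so a missing survey may be informative.

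The trial could therefore report no difference in adverse events from an analysis that cannot see deaths, while the two composites that do include deaths are driven mainly by retention or viral suppression.

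**Working it through.** **1. What feeds the comparison.** The comparison sentence lies between the description of the survey and the counselling offer to those who report an event. The following paragraph begins by setting record review apart from self-reported events, which labels the preceding material as self-report. The only use given for the record-review stream is ethics reporting. The text neither includes that stream in the compared risk nor excludes it. It also gives no denominator and no rule for a participant without a survey. By contrast, Hypothesis 5 does set such rules for efficacy: a missing viral load counts as non-suppressed, and a participant must be alive to count as a success.

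**2. The plan's own figures.** The protocol gives no number for adverse events, deaths or survey completion. The arm size comes from the Sampling section: "Allowing for 10% participant attrition, we would need to sample 175 participants per study arm". Check: 156 / 0.90 = 173.3, so 174 after rounding up, one below the stated 175. I use 175 as the arm size. The same section says the earlier study ascertained outcomes for 98.6% of participants, so 1.4% were missing. Neither 10% nor 1.4% is a survey non-response rate. They serve only as two illustrative levels.

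**3. Bounds on one arm's self-reported risk.** Let N = 175, u = share without a survey, r = event risk among those surveyed (assumed 5%).

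Lower bound (nobody missing had an event): r(1 − u). Upper bound (everybody missing had one): r(1 − u) + u.

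| u | Without survey | Events seen | Lower | Upper |
|---|---|---|---|---|
| 1.4% | 175 × 0.014 = 2.45 | 172.55 × 0.05 = 8.6 | 8.6/175 = 4.9% | (8.6 + 2.45)/175 = 6.3% |
| 10% | 175 × 0.10 = 17.5 | 157.5 × 0.05 = 7.9 | 7.9/175 = 4.5% | (7.9 + 17.5)/175 = 14.5% |

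**4. What a survey-only comparison misses.** Assume equal self-reported risk among those surveyed in both arms, with deaths of 2% in control and 5% in intervention: 175 × 0.02 = 3.5 and 175 × 0.05 = 8.75, so about 4 and 9. The survey-only risk difference is 0. The difference in deaths is 9/175 − 4/175 = 5.1% − 2.3% = 2.9 percentage points.

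**5. How a composite can mask it.** For illustration, take the Sampling section's 25% and 12.5% for 90-day absence as the share not retained under Hypothesis 4, and assume that the deaths in step 4 do not overlap with it. Failure is then 25% + 2% = 27% in control and 12.5% + 5% = 17.5% in intervention. The intervention looks 9.5 points better on alive-and-retained with two and a half times the assumed death rate. Absence at any time in 12 months is not the same as absence at closure, so this shows the mechanism and is not a forecast.

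**6. Precision.** With 9 against 4 deaths of 175 per arm, Fisher's exact p is 0.26. With 9 against 3 it is 0.14.

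**The case against.** The strongest reply is that the protocol does not say the comparison is survey-only. It refers to any adverse event, describes record review in the same section, and counts death as a severe event in Appendix N. A reader might infer that people who died are barred from contributing an event. The text does not support that: it leaves the source open, and the survey reading is only the natural one. This part of the reply stands and limits the wording of the point.

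A second reply is that event sources and denominators are commonly left to a statistical analysis plan, and that intention-to-treat is already stated. That covers much of the detail. It does not fully answer a protocol that states a between-arm harm comparison, appears to tie it to an instrument that cannot record death, and gives deaths no comparison of their own.

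Third, deaths are not ignored: vital status is traced and two between-arm tests count death as failure. This is true, but neither test isolates death or treats it as a harm. It is also fair that self-report suits the confidentiality harms that the protocol expects, which is a reason to keep it as a separate comparison.

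Fourth, a reader might infer from 25% against 12.5% that surveys will be lost unequally. Those figures are clinic absence, and people who leave care are traced and receive a tracing survey. If survey loss did follow them, more would be missing in control, the arm without group disclosure. They do not show that intervention-arm harm would be hidden.

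Finally, pooling record-review events with self-reports would bring its own bias: those events are seen mainly in people who attend clinic, so an intervention that improves attendance could appear to cause more of them. That objection stands and shapes the fix.

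**Conclusion.** The point holds in limited form, as a low-cost improvement that should be made. The compared adverse-event risk appears, on the natural reading, to come from the end-of-study survey, with its source and denominator not fixed. No section compares deaths between arms as a harm.

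The possible size depends on survey loss, which is not stated. At 175 per arm and an assumed 5% event risk among those surveyed, the uncertainty from missing surveys is slight at 1.4% loss (about 4.9% to 6.3%) and large at 10% (4.5% to 14.5%). The death counts are also assumed. What does not depend on them is that a survey-only comparison shows no difference in deaths, whatever that difference is.

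**What to change.** In Protocol VIII.F, Adverse Events (or in the analysis plan, with a reference from there):

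- State that safety is assessed over all randomised index participants.
- Add a separate between-arm comparison of all-cause death, using the vital status already collected from clinic records and tracing, for example by cumulative incidence.
- Keep self-reported adverse events as their own comparison. Report the number without a survey by arm, and the result when all of them are counted as events and when all are counted as non-events.
- Tabulate severe events found by record review by arm, separately and not pooled with self-reports, noting that their detection depends on clinic attendance.

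The cost is a few sentences and one more table, with no new data collection. The adverse-event risk will carry wider bounds. Deaths are likely to be few, so the mortality comparison will be imprecise and should be presented as an estimate with its interval, without treating a non-significant result as evidence of no difference.
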